##### The Working Alliance Inventory–Short Form Revised

The Working Alliance Inventory-Short Form Revised (WAI-SR) [36] measures therapeutic alliance, assessing agreement on the tasks of therapy, goals of therapy, and development of an affective bond. For example, item 1 asks “As a result of these sessions, I am clearer as to how I might be able to change.” The WAI–Short Form Revised (WAI-SR) demonstrated good psychometric properties in an initial validation, with internal reliability (α>.80) and convergent validity with related measures being good [37]. This measure is administered at baseline and 6 months.

#### Other Measurements

##### Measurements From the Embrace2 Device

Participants will have their physiological measurements continuously recorded, including EDA, actigraphy, and temperature, as described in the Interventions section. Actigraphy can be converted into resting time (ie, an approximation of sleep) and step counts. Reports of physiological measures from Empatica are in the form of CSV (comma-separated values) files that can be converted into dashboards and visual files using Splunk. Data transmitted to the research portal can also be examined for participant adherence to the device.

##### Ecological Momentary Assessment

Participants in the integrated mHealth intervention will be asked to report their stress levels in real time to identify periods when they are stressed or becoming unwell. Participants will receive a text message asking, “How stressed are you feeling now?” to be answered on a scale from 0 (not at all stressed) to 10 (very stressed), what they are doing, and/or how they are feeling. Participants will not respond to the text message, rather they will record their response on the Empatica Mate App, which is downloaded onto their phone. Text messages will be sent both according to an automated schedule and manually by the research psychologist. The event will be given a time stamp and recorded alongside participants’ physiological data.

##### Qualitative Interviews Regarding Attitudes Toward the unWIRED Intervention

Feedback will be obtained from participants and their case managers as to the acceptability and usefulness of the approach. For example, participants and case managers will be asked what they found helpful or challenging about using the mHealth device. This information will be sought either from focus groups or individual interviews. The transcribed responses will be thematically analyzed according to Braun and Clarke [38] by members of the research team.

##### Case Manager Report

A monthly report of participant engagement and use of the device will be recorded by the case manager.

### Outline of Study Processes

The following is an outline of the major components in administering the trial: recruitment, consent and initial assessment, administration, and trial conclusion.

#### Recruitment

Recruitment will primarily be managed by the research psychologist, who will explain and provide information to case managers and service managers at the clinical sites. Case managers will ask potential participants if they are interested in being involved. If they indicate interest, the research psychologist will contact them and answer any questions they may have regarding the project.

#### Consent, Randomization, and Initial Assessment

If a participant indicates interest in being involved, the research psychologist will ask for their written consent. Randomization will be determined by an external party who will communicate treatment condition to research staff. After consent and randomization, participants will be asked to complete a series of self-report questionnaires (see the Participant Self-Report, With Time Point, section). The psychologist will ask all participants to download the Empatica Mate App onto their phone and they will set up an Empatica account using a QR (Quick Response) code from the research portal. The Embrace2 device will be paired with the participant’s phone using Bluetooth. They will give the participant some basic instructions on how to operate the device, including how to charge it and keep it connected.

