### Randomization

Randomization will be conducted by an independent statistician not associated with the study. Randomly permuted blocks of 4 participants will be centrally generated using a computer-generated algorithm. The randomization sequence will be managed by staff independent of the project who will notify the clinical researcher of the randomization allocation. Participants, case managers, and clinician researchers at any one site will not be blinded as to allocation, as those in the integrated condition will regularly discuss the intervention with their case manager.

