##### The 21-Item Depression Anxiety and Stress Scale

The 21-item Depression Anxiety and Stress Scale (DASS-21) [31] is a measure of depression, anxiety, and stress over the previous week. Respondents rate each item on a 4-point Likert scale, ranging from 0 (not at all) to 3 (almost always). The DASS-21 has high reliability, a factor structure consistent with its subscales, and high convergent validity with other measures of anxiety and depression [32]. This scale is administered at baseline and 6 months.

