### Power Calculations and Statistical Analysis

The primary outcome for this study is to compare changes in treatment-related outcomes before and after the intervention for participants enrolled in the integrated versus unintegrated conditions. There are currently no trials examining the augmentation of treatment with an mHealth device, so sample size estimations are made using general calculations. Assuming a moderately sized advantage of the integrated (ie, unWIRED) versus unintegrated device on outcomes (effect size=0.5, 80% power, and a 2-tailed α of .05), we will require 63 participants per group.

The RCT component generally compares measures of mental health, distress, and functioning between the conditions, adjusted for baseline scores. For example, this analysis may focus on an intent to treat using a hierarchical linear model (HLM) to test the differential effects of the two treatment conditions, because this method allows the number of observations to vary between participants and handles missing data by calculating estimates of trajectories using maximum likelihood estimation. Fixed effects could be tested for intervention condition and time of assessment. Random effects in the unstructured models provide an index of the relative effects of the treatments over time. Fixed effects parameters may be tested with the Wald test (*t* test, *P*<.05, 2-sided) and 95% confidence intervals. Analyses will focus on the primary outcomes (ie, CGI scores) and secondary outcomes (eg, APQ6, BASIS-24, DASS-21, PSQI, and AQoL-8D) between the unWIRED group and the active control group, with the main outcome points being at the 6-month follow-up relative to baseline. All results are based on estimated mean values derived from HLM analyses. The within-subjects analysis will be comprised of linear fixed effects models using physiological measurements (ie, sleep, activity, and EDA) to predict measures of mental health, distress, and functioning. Baseline variables may be used as covariates when analyzing individual and between-group differences (eg, age, illness severity, treatments, and personality differences). Thematic analysis [38] will be used to examine individual and group qualitative feedback regarding the acceptability of the mHealth device and the unWIRED intervention for participants and case managers; there will be approximately 10-20 participants in the patient and clinician groups.

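### Baseline self-report questionnaires come after randomisation in an unblinded trial, so the baseline scores for the self-report outcomes can be affected by allocation

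*Protocol article*

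**What the plan says.** The protocol article, under Consent, Randomization, and Initial Assessment, first has the research psychologist obtain written consent. Next, "Randomization will be determined by an external party who will communicate treatment condition to research staff". The sentence after that reads "After consent and randomization, participants will be asked to complete a series of self-report questionnaires". Pairing the device and downloading the app are described last.

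Under Randomization the article adds: "Participants, case managers, and clinician researchers at any one site will not be blinded as to allocation".

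The instruments given at this first assessment are BFI-10, DASS-21, BASIS-24, APQ6, AQoL-8D, PSQI and WAI-SR. Their own sections call this administration the baseline; for the DASS-21, "This scale is administered at baseline and 6 months".

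Under Power Calculations and Statistical Analysis, "The RCT component generally compares measures of mental health, distress, and functioning between the conditions, adjusted for baseline scores", "with the main outcome points being at the 6-month follow-up relative to baseline". The secondary outcomes named there as examples are APQ6, BASIS-24, DASS-21, PSQI and AQoL-8D, all self-report. Baseline variables, personality among them, may serve as covariates.

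**The concern.** A baseline score is safe to adjust for because allocation cannot have caused it. Here the score is collected once allocation exists and the staff running the assessment have been told it. The arms differ in whether the case manager sees the participant's arousal, sleep and activity. A participant who learns which arm applies could plausibly answer items on distress, sleep or working alliance differently.

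Two things are at stake. First, an allocation-driven shift at baseline feeds into any comparison that adjusts for baseline or measures change from it. Second, someone who disengages on hearing their arm is already randomised but has no baseline score, so missing baselines could depend on arm.

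This is a stated sequence, not a detail left to a fuller document. An analysis plan could not fully repair it, because no self-report score from before randomisation would exist.

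**Working it through.** **Order of events, from the documents**

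| Step | What the article says | Section |
|---|---|---|
| 1 | Written consent | Consent, Randomization, and Initial Assessment |
| 2 | External party determines allocation and tells research staff | same |
| 3 | Self-report questionnaires | same |
| Throughout | Participants, case managers and clinician researchers unblinded | Randomization |
| Analysis | Adjusted for baseline; 6 months relative to baseline | Power Calculations and Statistical Analysis |

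No section places these questionnaires before randomisation or withholds the allocation until they are done.

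**The plan's own figure.** With effect size 0.5, 80% power and two-sided alpha 0.05, n per arm = 2 × (1.960 + 0.842)² / 0.5² = 62.8, so 63, as stated. This point does not change it; 63 per arm is used below only to set a scale.

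**Illustration.** The documents give neither the shift nor the correlation, so both are assumed. Let
- δ = shift in one arm's baseline mean caused by allocation, in SD (0.1 to 0.3)
- φ = shift in that arm's reporting at 6 months from the same cause, in SD
- r = baseline to 6-month correlation (0.4 to 0.6), with equal SDs at both times, so the adjustment slope is r.

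Bias in the baseline-adjusted difference = φ − rδ. Bias in the change-from-baseline difference = φ − δ.

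*No shift at follow-up (φ = 0).* The size of the adjusted bias is rδ:
- 0.4 × 0.1 = 0.04 SD
- 0.5 × 0.2 = 0.10 SD
- 0.6 × 0.3 = 0.18 SD

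A change-score comparison would carry the whole δ, 0.1 to 0.3 SD.

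*Full shift persists (φ = δ).* The adjusted bias is δ(1 − r), with the opposite sign: from 0.1 × (1 − 0.6) = 0.04 SD to 0.3 × (1 − 0.4) = 0.18 SD. The change-score bias is zero.

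*Effect on the test, φ = 0, r = 0.5, 63 per arm.* The standard error is √(1 − 0.5²) × √(2/63) = 0.154 SD.

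| δ | Bias | Two-sided type I error (nominal 5%) | Power for a true 0.5 SD effect if the bias opposes it (90.0% without bias) |
|---|---|---|---|
| 0.1 | 0.05 | 6.2% | 83.1% |
| 0.2 | 0.10 | 9.9% | 73.6% |
| 0.3 | 0.15 | 16.3% | 62.1% |

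**The case against.** The case for leaving this alone has several parts, and much of it limits the point.

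- **The primary outcome.** A reader might infer that the main trial comparison is biased. The documents do not support that. The CGI is rated by blinded clinicians, and none of these questionnaires is said to feed it. The only route in would be an optional self-report covariate such as BFI-10. This stands.
- **Every secondary analysis.** A reader might extend the problem to all of them. SOFAS is rated by case managers, blinded staff and chart review, and the within-subjects analysis is not a comparison between arms. This stands.
- **Participants already know their arm.** This is tempting, but it is an inference: the article says when research staff are told, not when the participant is. What it does show is that nothing prevents disclosure first. The risk is documented; its occurrence is not.
- **Look-back periods.** DASS-21, BASIS-24 and AQoL-8D cover the previous week, PSQI 7 days and APQ6 a month, so the period reported on largely precedes allocation. That limits a shift but does not exclude one, since the answers are still given afterwards.
- **Size.** Dividing 0.04 to 0.18 by 0.5 gives 8% to 36%, which might be read as a property of the plan. It is not. The shift is assumed and could be zero, the formula assumes no shift at follow-up, the hierarchical model is offered only as an example, and 0.5 is a generic effect size not tied to these scales. If the shift persists, the affected baseline even removes part of a reporting artefact at 6 months.
- **Missing baselines.** The documents contain no evidence that this will happen. The order only makes it possible.

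None of this gives a reason to keep the stated order.

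**Conclusion.** The concern holds, within limits. The stated sequence lets allocation influence the baseline values of the self-report secondary outcomes, WAI-SR and self-report covariates such as BFI-10, and lets missing baselines depend on arm. The blinded CGI primary outcome is not directly affected, and no section shows that baseline CGI or SOFAS ratings follow randomisation.

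The figure of 0.04 to 0.18 SD is an illustration. It rests on an assumed shift of 0.1 to 0.3 SD, none at follow-up, and an assumed correlation of 0.4 to 0.6. With no shift the bias is zero; with a persisting shift it changes sign. Because the documents allow neither size nor direction to be known, it could not be corrected afterwards. That, and the ease of prevention, is why the order should be changed even though its reach is secondary.

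**What to change.** Amend Consent, Randomization, and Initial Assessment so that the baseline self-report questionnaires are completed after written consent and before the allocation is generated or disclosed to research staff or participants. The external party releases the allocation only once baseline is recorded as complete; device set-up follows. If practice already withholds the allocation until the questionnaires are done, the section should say so.

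The cost is small and logistical: a completion check before release, and possibly a short wait before the device is set up. The instruments, sample size and interventions are unchanged.

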#### Trial Administration

Data will be collected from the Embrace2 in a continuous and ongoing manner for all participants. Case management and treatment will continue as per usual in the community mental health services. Case managers of participants in the integrated unWIRED arm will receive training on how to use the mHealth device and dashboard to monitor a participant’s mental state. Research staff will monitor the extent to which there are data uploaded from the device based on the Empatica Research Portal. If unWIRED participants are observed to have minimal adherence over consecutive days, the research psychologist can contact each participant to determine the reason for the disconnection and attempt to restore the device. During the trial, the research psychologist may send EMA text messages to the unWIRED participants to determine stress levels and their responses will be visible on the Empatica Research Portal. EMA messages will be sent according to a schedule and can also be sent manually by the research psychologist. Physiological data from each unWIRED participant’s previous day will be displayed on the Splunk dashboard, showing their activity, rest, and EDA. A link to the dashboard will be provided to case managers so they can view the information on their work computer. Case managers will use the information from the dashboard to enhance their clinical decisions. Clinical staff and participants will be encouraged to discuss data recorded from the device during their meetings and to include this information in their collaborative care plan. Case managers will be provided with a basic manual for interpreting the dashboard; however, a clinical response will be left to their clinical judgement. Throughout the trial administration, clinical staff will be asked to report on their participant’s ongoing functioning and distress, as described in the Assessments of Mental Deterioration section. The research team can provide support to case managers as needed.

#### Trial Conclusion

After the 6-month enrollment in the study, or earlier if a participant asks to withdraw, all participants will once again be asked complete the self-report questionnaires that were administered during the initial appointment (see Participant Self-Report, With Time Point, section). Researchers will ask participants to remove their devices and return them to administrative staff at their clinical site. Each participant will be registered as having “completed” the trial on the Empatica portal, and clinical staff will be informed that they are no longer in the trial. Qualitative interviews may be used after the trial to examine both participant and case manager experiences with the integrated mHealth device. See Figure 2 for the RCT CONSORT-EHEALTH flow diagram.

**Figure 2 figure2:**
[figure not shown]
Outline of measurements for the randomized controlled trial. APQ6: Activity and Participation Questionnaire; AQoL-8D: Assessment of Quality of Life-8 Dimension; BASIS-24: Behaviour and Symptom Identification Scale-24; BFI-10: 10-item Big Five Inventory; CGI: Clinical Global Impression Scale; DASS-21: 21-item Depression Anxiety and Stress Scale; EDA: electrodermal activity; EMA: ecological momentary assessment; mHealth: mobile health; PSQI: Pittsburgh Sleep Quality Index; SOFAS: Social and Occupational Functioning Assessment Scale; WAI-SR: Working Alliance Inventory–Short Form Revised.

### Safety Monitoring

This study will be overseen by senior psychiatrists (AH, BK, and JS) who have extensive clinical experience in youth mental health. The participants will have case managers who are mental health professionals working with them on a weekly basis. Adverse events can be reported by either the participants or their case managers and reviewed by an investigational team. Participants will be prompted to report any adverse events. All adverse events will be recorded in the adverse event log in the participant case report form, including the seriousness, severity, relationship to study product, duration, and outcome. Steps will be taken according to the adverse reaction decision tree. In all cases, researchers will maintain contact with participants who experience an adverse event until it has been resolved and symptoms disappear. If required, they will also be asked to notify their general practitioner or primary care doctor. Standard Operating Procedures will be in place to insure the trial is conducted in accordance with Good Clinical Practice. The project will have an independent data safety monitoring board (DSMB) composed of health professionals, researchers, and IT experts who will meet every 4 months. The project will have regular reviews and meetings to determine the safety and integrity of the data.

### Data Collection, Use, and Privacy

Data will be collected by the research team and will be coded so that they will not be identifiable to anyone other than the research team. Data will be collected manually through self-report, interview notes, and EMAs and automatically through the mHealth device. The physiological data will be transmitted to the Empatica interface and downloaded to the project system within a day of recording. However, all data going to Empatica will be deidentified and coded. All data, once converted to electronic format where applicable, will be backed up on a password-protected computer hard drive. Source documents will be kept in participant files, which will be stored in a locked cabinet in a locked room. Data from measures will be entered into a password-protected electronic database on a secure health network drive and backed up onto a password-protected University of Sydney system. No uncoded or identifiable data will be stored outside of the hospital research site. A DSMB, composed of researchers in eHealth, psychiatrists, and information officers will meet to discuss the data management processes associated with this study.

Physiological data will be uploaded onto the secure website of Empatica Inc via its website in the United States. Data will then be retrieved and downloaded onto a University of Sydney server and analyzed within the secure university environment. Information will be returned to treating clinicians operating within NSW Health firewalls. The initial data are controlled by Empatica; they will then be transferred to University of Sydney and ESE (Engineering Und Software-Entwicklung GmbH) servers, which are assisting with data management. Data flow through servers domiciled in either the United States or the European Union is allowed in NSW Health [39] and does not breach the NSW Health Records and Information Privacy Act 2002 [40].

### Power Calculations and Statistical Analysis

The primary outcome for this study is to compare changes in treatment-related outcomes before and after the intervention for participants enrolled in the integrated versus unintegrated conditions. There are currently no trials examining the augmentation of treatment with an mHealth device, so sample size estimations are made using general calculations. Assuming a moderately sized advantage of the integrated (ie, unWIRED) versus unintegrated device on outcomes (effect size=0.5, 80% power, and a 2-tailed α of .05), we will require 63 participants per group.

The RCT component generally compares measures of mental health, distress, and functioning between the conditions, adjusted for baseline scores. For example, this analysis may focus on an intent to treat using a hierarchical linear model (HLM) to test the differential effects of the two treatment conditions, because this method allows the number of observations to vary between participants and handles missing data by calculating estimates of trajectories using maximum likelihood estimation. Fixed effects could be tested for intervention condition and time of assessment. Random effects in the unstructured models provide an index of the relative effects of the treatments over time. Fixed effects parameters may be tested with the Wald test (*t* test, *P*<.05, 2-sided) and 95% confidence intervals. Analyses will focus on the primary outcomes (ie, CGI scores) and secondary outcomes (eg, APQ6, BASIS-24, DASS-21, PSQI, and AQoL-8D) between the unWIRED group and the active control group, with the main outcome points being at the 6-month follow-up relative to baseline. All results are based on estimated mean values derived from HLM analyses. The within-subjects analysis will be comprised of linear fixed effects models using physiological measurements (ie, sleep, activity, and EDA) to predict measures of mental health, distress, and functioning. Baseline variables may be used as covariates when analyzing individual and between-group differences (eg, age, illness severity, treatments, and personality differences). Thematic analysis [38] will be used to examine individual and group qualitative feedback regarding the acceptability of the mHealth device and the unWIRED intervention for participants and case managers; there will be approximately 10-20 participants in the patient and clinician groups.

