mHealth devices have been used effectively for managing and monitoring physical conditions such as cardiovascular disorders, diabetes, and obesity [18]. More recently, continuous data from an mHealth device has shown promise in predicting signs of stress and mental deterioration. For example, Sano and colleagues [19] examined whether physiological and behavioral measures collected by wearable sensors and mobile phones could predict stress and poor mental health in a large student sample (N=201). They used machine learning, a subfield of artificial intelligence, to analyze the multimodal data. The mHealth devices classified students into high- or low-stress groups 78.3% of the time and as experiencing high or low mental health 87% of the time. Cella and colleagues [20] used an mHealth device to compare heart rate, EDA, and movement for 30 participants with schizophrenia in the community and 25 controls. Compared to controls, participants with schizophrenia showed lower heart rate variability, movement, and functioning, consistent with autonomic dysregulation. Positive symptoms were also correlated with parasympathetic dysregulation. Most recently, Cella and colleagues [21] asked participants with first episode psychosis to wear an mHealth device to continuously measure their heart rate variability and EDA while self-reporting psychotic symptoms. They found higher EDA during periods where participants were experiencing psychosis.

The use of an mHealth device in younger adults with mental illness over extended periods has yet to be tested. This age group is more likely to be “tech savvy” and they are at high risk of developing severe mental illness. Pilot data indicate 15 out of 19 young adults with severe mental illness wore an mHealth device for greater than two weeks, and information regarding each participant’s activity, sleep, EDA, and subjective stress was reliably collected during this period [22]. The next challenge is establishing if this information is clinically useful and predicts relapse. This protocol describes using information from an mHealth device streamed to both case managers and patients to allow them to independently monitor and then collaborate to manage any early warning signs (see Figure 1).

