### Participants

The study will recruit 126 youths aged 18-25 years with a severe mental illness drawn from youth community mental health services in Western Sydney and Sydney Local Health Districts in New South Wales (NSW), Australia, where BK, JS, and AH are senior psychiatrists. Admission to these services is determined by participants experiencing moderate to severe mental illness that impairs functioning. All participants at these sites will be receiving case management for their mental illness, including regular medication monitoring and/or psychosocial treatments consistent with Australian and New Zealand College of Psychiatry guidelines. Participants will not be paid; however, they can be reimbursed for costs associated with participation, such as travel expenses or mobile phone credit.

Inclusion criteria are (1) being a current community mental health service patient, (2) aged 18-25 years, (3) having a confirmed diagnosis of serious mental illness, including schizophrenia spectrum disorders, bipolar affective disorder, severe major depressive disorder, anxiety disorder, and/or personality disorder, and (4) having the capacity to consent to the study.

Exclusion criteria are (1) being non-English speaking, (2) having greater than mild developmental disability, and (3) having an inability to comply with either the requirements of informed consent or the treatment protocol.

Substance use will not be an exclusion criterion, as the effects of stress due to substance withdrawal and self-medication are important factors in relapse. It is also important to keep the study population ecologically similar to the clinical population.

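### The 126 to be recruited equals the number needed with complete outcome data, so the stated 80% power has no allowance for loss of the 6-month outcome

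*Protocol article*

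**What the plan says.** Under Power Calculations and Statistical Analysis, the protocol article says that no earlier trial was available to inform the size, "so sample size estimations are made using general calculations". The inputs and the result are stated together: "effect size=0.5, 80% power, and a 2-tailed α of .05), we will require 63 participants per group".

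The Participants section sets the target: "The study will recruit 126 youths aged 18-25 years with a severe mental illness". The Methods part of the abstract gives the same total. The Randomization section describes two arms filled from permuted blocks of 4, which fits equal allocation.

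Three other places bear on whether all 126 will supply a 6-month outcome:

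- Trial Conclusion has participants complete the closing questionnaires "After the 6-month enrollment in the study, or earlier if a participant asks to withdraw". They then return the device, and clinical staff are told that they have left the trial.
- The analysis section favours a hierarchical linear model (HLM), partly because it copes with missing data. It sets the main comparison at 6 months relative to baseline.
- Under Assessments of Mental Deterioration, the CGI (primary) and the SOFAS are rated monthly, and the Chart Reviews section says that research staff make these ratings mainly from electronic records.

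**The concern.** The number required and the number recruited are the same, so the calculation has no margin. It assumes that every randomised participant supplies the 6-month outcome, while other sections of the article expect that some will not. This is not a detail left to an analysis plan that is not shown, because the article itself prints the inputs, the required number and the recruitment target.

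At stake is how a null result would be read. A reader would set it against an 80% chance of detecting a moderate effect, although the real chance depends on a loss rate and a baseline correlation that the article does not state. The article also does not say what happens to the primary rating when a participant stops the device or leaves. That matters because a chart-based rating can be made whether or not the device is worn, so some of the loss is avoidable.

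**Working it through.** **Inputs.** Standardised difference d = 0.5, two-sided alpha 0.05, power 80% and 63 per group come from Power Calculations and Statistical Analysis. The total of 126 comes from Participants. Loss rates of 10%, 20% and 30% and baseline–outcome correlations r of 0.3, 0.5 and 0.6 are my assumptions, because the article gives neither.

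**Step 1: reproduce the stated figure.** By the normal approximation, n per group = 2(1.96 + 0.8416)² / 0.5² = 62.8, rounded up to 63, with 80.1% power at 63. The t-test version needs 63.8, so 64, and gives 79.5% at 63. That gap is one participant per group and is immaterial. No loss term is needed to arrive at 63, and 2 × 63 = 126.

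**Step 2: unadjusted power with loss.** Set n = 63 × (1 − loss) per group and take two-sample t-test power at d = 0.5. The normal approximation gives values up to one point higher (75.9%, 70.9% and 65.1% for the three loss rates).

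**Step 3: power with baseline adjustment.** Adjusting for baseline reduces the residual SD to √(1 − r²), so the effective difference is 0.5 / √(1 − r²): 0.524 at r = 0.3, 0.577 at r = 0.5 and 0.625 at r = 0.6. This takes 0.5 as standardised on the unadjusted outcome SD.

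| Loss | n per group | Unadjusted | r = 0.3 | r = 0.5 | r = 0.6 |
|---|---|---|---|---|---|
| 0% | 63 | 79.5% | 83% | 90% | 94% |
| 10% | 56.7 | 75% | 79% | 86% | 91% |
| 20% | 50.4 | 70% | 74% | 82% | 87% |
| 30% | 44.1 | 64% | 68% | 76% | 83% |

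**Step 4: break-even.** In the normal approximation, adjustment makes up for a loss exactly when 1 − r² = 1 − loss, so r = √loss: 0.32 at 10%, 0.45 at 20% and 0.55 at 30%. Below those correlations the design falls short of 80%; above them it does not.

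**Limit of the model.** Step 2 treats a participant without a 6-month rating as contributing nothing. The HLM would still use that participant's earlier monthly ratings, so the loss columns lean towards pessimism. The article gives no information from which that gain could be quantified.

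**The case against.** The strongest reply is that the analysis described is not a bare two-sample test. It adjusts for baseline and uses incomplete series through maximum likelihood, and Steps 3 and 4 show that a moderate correlation would restore 80%. This stands, and it rules out saying that the trial lacks 80% power. It does not rescue the statement in the article, which takes no credit for adjustment and gives no correlation from which a reader could check it.

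Four stronger readings are tempting, and the document does not support them:

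- *The pilot shows a 21% dropout rate.* The pilot result is that "15 out of 19 young adults with severe mental illness wore an mHealth device for greater than two weeks". The other 4 of 19 did not wear the device for that long. This describes adherence over about two weeks, and the article does not say that those participants were lost. Someone who stops wearing the device can still be rated from the record.
- *Follow-up of the primary outcome ends at withdrawal.* Trial Conclusion ties the closing questionnaires, device return and trial status to withdrawal. No section says that chart-based CGI ratings stop, and none says that they continue. The point is open.
- *Non-wear dilutes the effect to 0.5 × 15/19 = 0.395, with power of 59%.* This assumes that 0.5 is the effect in wearers only. The article puts 0.5 forward as the advantage of the integrated over the unintegrated device and does not restrict it to wearers, so the discount may count non-adherence twice.
- *Early-exit questionnaires will stand in for 6-month scores.* The article does not say so, and the dating of off-schedule assessments is ordinary analysis-plan detail.

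**Conclusion.** The point holds in limited form. The arithmetic behind 63 per group is correct, but 63 is the number with complete outcome data. Recruiting exactly 126 leaves no margin in a trial that itself provides for early withdrawal and missing data. On the stated calculation, power is about 75%, 70% and 64% at assumed losses of 10%, 20% and 30%. With baseline adjustment at 20% loss it ranges from about 74% (r = 0.3) to 87% (r = 0.6), so whether 80% is reached turns on two quantities that the article does not give. The adjusted figures rest on 0.5 being standardised on the unadjusted SD, and all the loss figures rest on a participant without a 6-month rating adding no information. The defect is an unsupported power statement that can be corrected without changing the size of the trial.

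**What to change.** Keep 126 and make two changes of wording.

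1. Restate the power for 126 randomised over a stated range of loss, both unadjusted and for the planned baseline-adjusted comparison at stated correlations. For example: *With 126 randomised and 10% to 30% of 6-month outcomes missing, power for a standardised difference of 0.5 is about 75% to 64% unadjusted; at 20% missing it is about 74%, 82% and 87% after baseline adjustment for assumed correlations of 0.3, 0.5 and 0.6.* The sponsor should put in its own expected loss and say where the assumed correlation comes from. The pilot wear figure should not serve as the loss rate. Any calculation for a diluted effect should be labelled as an assumption.

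2. Distinguish stopping the device from withdrawing consent for access to records. State that participants who only stop the device keep their monthly blinded chart-based CGI and SOFAS ratings to month 6 and stay in the intention-to-treat analysis.

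The cost is a few extra chart reviews and a stated power less favourable than 80% before adjustment. No additional participants are needed.
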